#### **8.1.4. Safety Analysis**

Safety endpoints include adverse events, laboratory data, and concomitant medications.

Adverse event verbatim terms recorded on the CRF will be mapped to preferred terms using the Medical Dictionary for Regulatory Activities (MedDRA).

A treatment emergent adverse event (TEAE) is defined as any adverse event with an onset date on or after date of first dose of study drug, or any ongoing event on date of first dose that worsens in severity after date of first dose. Only TEAE's with an onset date prior to date of last dose + 30 days will be tabulated in the summary tables.

TEAEs will be summarized for overall incidence, worst reported severity, and relationship to study treatment according to system organ class and preferred term.

Laboratory variables will be categorized according to the CTCAE v3.0 and will be summarized using mean change from baseline and shift in category from baseline.

All concomitant medications collected on the CRF's will be mapped to the WHO dictionary. Prior and concomitant medications will be summarized separately by ATC Level and Preferred Term.

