### **3. STUDY DESIGN**

#### **3.1. Overview of Study Design**

This is a Phase 2, non-randomized, sequential-cohort, open-label, single-stage, safety and efficacy study, with an initial cohort of subjects enrolled onto the Intermittent 5&9 regimen, and then a 2nd cohort of subjects enrolled onto the daily regimen. Enrolment into Cohort 2 will not begin until enrolment into Cohort 1 has completed.

The estimated length of the study is 40 months for subject accrual and treatment. This study consists of a Pre-Treatment Period (screening and baseline evaluations), a Study Treatment Period, an optional Treatment Extension Period, and a Post-Treatment Period (including an end-of-treatment visit and an extended follow-up period). Throughout the study, AEs will be recorded as volunteered. Adverse events will be graded according to the NCI CTCAE v3.0. A copy of this grading scale will be provided to the study sites upon request, or it can be accessed at <http://ctep.cancer.gov/reporting/ctc.html>. All doses of GSK1363089 are to be administered on an empty stomach.

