### **3.1.2. Study Treatment Period**

Treatment will be administered on an outpatient basis. Previously reported AEs and potential risks for GSK1363089 are described in Section 5.11. Dose modifications for GSK1363089 are described in Section 3.4. No investigational or commercial agents or therapies other than those described in Section 4.4 may be administered with the intent to treat a subject's malignancy.

GSK1363089 will be administered at a dose of 240 mg on an Intermittent 5&9 dosing schedule in Cohort 1; and at a dose of 80 mg on a daily dosing schedule in Cohort 2. Each treatment cycle will be 2 weeks in duration. The 8-week Study Treatment Period will consist of four 2-week treatment cycles. Laboratory evaluations and physical examinations will be conducted before each dosing cycle. GSK1363089 treatment will be stopped if there is disease progression at any time.

In-patient hospitalization is not required for study treatment and assessments if the subject is adequately observed and procedures are performed as specified herein.

At specified timepoints during the treatment period, AEs will be solicited by asking the subject, "Are you having any new symptoms?" Answers will be recorded on the AE case report form (CRF) page. Tumor assessment will be performed at the end of the Study Treatment Period (8 weeks).

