#### **3.5. Requirement for Collection of Paired Tumor Biopsies**

Following the implementation of protocol Amendment 4.0, the collection of fresh, paired tumor biopsies will become a requirement rather than an option, to allow the assessment of the expression of pharmacodynamic markers of GSK1363089 activity, in particular relating to the c-MET pathway (e.g. total c-MET, phospho-MET and downstream markers).

After the first 6 subjects have been enrolled under Amendment 4.0 and have had paired tumor biopsies collected, enrolment will be put on temporary hold, while the safety and acceptability of collecting paired biopsies, plus the pharmacodynamic data, are reviewed

by GSK. If there are no safety concerns, and the pharmacodynamic objective with respect to c-MET has not been met, then subject enrolment will recommence and continue until the target number of subjects for Cohort 2 has been reached.

The safety and pharmacodynamic data for the paired tumor biopsies will continue to be reviewed on an ongoing basis. If a safety concern with obtaining the biopsies should ever arise and/or the pharmacodynamic objective with respect to c-MET has been met, then paired biopsies will no longer be required in this study. This will be communicated to the sites and IRBs by letter from GSK or its designee.

If any subject is not able to provide the second biopsy (i.e. at Day 5-8), then that subject will be allowed to continue on study and will be eligible for inclusion in the safety and efficacy assessments. However, if by so doing, this would prevent at least 12 subjects being enrolled who do provide paired biopsies, then an extra subject will be enrolled.

Instructions for the collection of paired tumor biopsies are provided in Section 5.9.2 and the Pharmacodynamic Laboratory Manual.

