#### **5.3.1.3. Post-Dose Evaluations**

- Vital signs (5-minute sitting BP, pulse, respiratory rate, oral temperature) taken within approximately 30 minutes before the PK sampling timepoint
- PK and pharmacodynamic blood samples collected at 4 hours post-dose (see Section 5.7)
- Concomitant medications
- Adverse events (see Section 7.1.1)

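### Adverse-event collection before the first dose is inconsistent, so harms of the mandatory baseline biopsy are captured only passively, although enrolment pauses after six subjects to judge biopsy safety

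*Combined protocol and SAP*

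**What the plan says.** Under Amendment 4.0, subjects newly enrolled in Cohort 2 must give two fresh tumor biopsies, one before any dose and one between Days 5 and 8 (Sections 3.5 and 5.9.2). Once six such subjects have had both, enrolment stops temporarily "while the safety and acceptability of collecting paired biopsies, plus the pharmacodynamic data, are reviewed" by the sponsor. Review then continues, and a safety concern at any time ends the requirement.

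On recording, Section 3.1 states the general rule: "Throughout the study, AEs will be recorded as volunteered". It also defines the study's extent: "This study consists of a Pre-Treatment Period (screening and baseline evaluations), a Study Treatment Period" and the later periods. Section 3.1.2 describes active questioning: "At specified timepoints during the treatment period, AEs will be solicited by asking the subject". Section 7.2.1 makes serious adverse events (SAEs) reportable over the course of the study whatever treatment was received. It gives an end to AE reporting (the 30-day visit) but no start.

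On analysis, Section 8.1.4 defines a treatment-emergent adverse event (TEAE) as "any adverse event with an onset date on or after date of first dose of study drug". A complaint already present when dosing begins counts only if it later becomes more severe. For the summaries, the section sets this limit: "Only TEAE's with an onset date prior to date of last dose + 30 days will be tabulated in the summary tables". Section 8.1.1 limits the safety population to subjects with at least one dose, and Section 5.10.2 replaces subjects who receive none.

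**The concern.** The protocol makes an invasive procedure a condition of entry and treats its safety as a reason to stop requiring it. Half of those procedures take place before the first dose, where the visit schedule has no AE item and the planned tables largely do not reach.

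Sites usually work from the visit lists and the schedule of assessments. A site that does so would record bleeding or pain after the baseline biopsy only if the subject mentioned it, or if it was serious. Another site, relying on Section 3.1, might record it routinely. The sponsor would then judge the procedure on uneven data. The subject with the worst first-biopsy experience, who never goes on to treatment, would be missing from every planned safety summary.

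**Working it through.** No figure in the protocol bears on this point, so the check is a comparison of sections followed by an illustration of size.

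**Is a non-serious complication of the baseline biopsy covered?**

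| Place | What it provides | Baseline biopsy covered? |
|---|---|---|
| 3.1 | Volunteered AEs, whole study including the Pre-Treatment Period | Yes, passively |
| 3.1.2 | Active questioning in the treatment period | No |
| 5.2 | Screening and baseline lists, no AE item | No |
| 5.3.1.1 | Day 1 pre-dose list, no AE item | No |
| 5.3.1.3 | Day 1 post-dose list, first AE item | Not at the time of the biopsy |
| Appendix A | AE row empty at Screening and Baseline, first mark at Day 1 | No |
| 7.1.1 | AE defined for a subject given a product | Unclear before dosing |
| 7.2.1 | SAEs during the study; AE window with an end but no start | SAEs yes; non-serious AEs unclear |
| 8.1.4 | TEAE tables | Only if ongoing at first dose and then worse |
| 8.1.1, 5.10.2 | Dosed subjects analysed, undosed replaced | Never-dosed subjects left out |

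The general rule in 3.1 and the schedule in 5.2, 5.3.1.1 and Appendix A therefore point in different directions, and nothing says which governs.

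Two further points follow from the text. Section 7.1.1 grades relationship only to the investigational drug. Events after the second biopsy do fall in the TEAE window, but the tables described would not identify them as biopsy events. Also, Section 3.5 counts the six as subjects with both biopsies. Read literally, a subject who stopped after a complicated first biopsy is not one of them.

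**Size in the worst case**

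Inputs: 6 subjects at the hold and 2 biopsy procedures each (Section 3.5), so 12 procedures, 6 of them before dosing. The protocol gives no complication rate. I assume a non-serious complication rate p of 10% per procedure, with a range of 5% to 20%, and independence between procedures.

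The chance of seeing at least one event in n procedures is 1 − (1 − p)^n.

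| p | Second biopsies only, n = 6 | Both biopsies, n = 12 |
|---|---|---|
| 5% | 1 − 0.95^6 = 26% | 1 − 0.95^12 = 46% |
| 10% | 1 − 0.90^6 = 47% | 1 − 0.90^12 = 72% |
| 20% | 1 − 0.80^6 = 74% | 1 − 0.80^12 = 93% |

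If no event is seen, the one-sided 95% upper limit on the rate is 1 − 0.05^(1/n). That is 39% for 0 of 6 and 22% for 0 of 12. At the target of 12 paired subjects in Section 3.5, the procedures affected are 12 of 24.

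**The case against.** A reader might infer that baseline-biopsy complications are not recorded at all, or that only serious ones are. The documents do not support that. Section 3.1 covers volunteered AEs throughout a study that includes the Pre-Treatment Period, and Section 7.2.1 sets no first-dose start. What is missing before dosing is scheduled or solicited collection.

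A reader might also infer that the six-subject review must lack these events because the TEAE tables do. Section 3.5 does not tie the review to those tables; it names no data source. Section 10 adds monthly safety-team meetings and at least quarterly review of all available safety data with investigators. Section 8.1 leaves analysis details to a separate plan, so silence in 8.1.4 does not prove that no listing is intended.

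Nor is the TEAE definition an error. Starting at first dose is conventional for drug safety. It is also speculative that biopsy events would be blamed on the drug, since 7.1.1 lets the investigator attribute an event to another cause.

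Other pre-dose data could hint at a complication: concomitant medications at screening and baseline, and vital signs and a symptom-directed examination before the first dose. They do not replace an AE record.

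The probabilities above assume no capture at all, which Section 3.1 contradicts. They bound the loss under the assumed rates and do not estimate it.

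These objections limit the claim but do not remove it. The sections still disagree, the data for the hold are unnamed, and never-dosed subjects remain outside every safety analysis described.

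**Conclusion.** The point holds as an inconsistency with a cheap remedy. Followed as scheduled, the protocol collects non-serious harms of the mandatory baseline biopsy only if subjects volunteer them. The tables in 8.1.4 omit any that do not worsen after first dose, and subjects whose complication prevents dosing drop out of the safety analysis and are replaced.

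In the worst case, 6 of the 12 procedures at the hold carry no non-serious AE data. The chance of seeing at least one event is then 47% instead of 72% at an assumed 10% rate. The actual loss lies between none and this, depending on how much is volunteered. The contrast also rests on independence between the two biopsies in one subject. The drug-safety definition and the efficacy design are unaffected.

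**What to change.** - Align Sections 3.1, 5.2, 7.2 and Appendix A so that procedure-related AEs are collected from the start of the baseline biopsy, with an AE item at the pre-dose visits.
- In Section 8.1.4, keep the TEAE definition and add a separate table or listing of biopsy-related AEs by biopsy (baseline; Day 5 to 8). Base it on all biopsied subjects, including those never dosed.
- In Section 3.5, state that the six-subject review and the ongoing review use that table or listing.

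The cost is slightly more AE recording during screening, on the existing AE page, and one extra table.

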### **Statistical Methods**

The primary efficacy endpoint is objective response rate (ORR). ORR will be estimated for the safety and the evaluable populations. A corresponding exact 95% confidence interval will be calculated.

Secondary efficacy endpoints are disease stabilization rate (DSR), progression-free survival (PFS), duration of stable disease, and duration of overall survival (OS). DSR will be summarized using a point estimate of the proportion and the exact 95% confidence interval. PFS, OS, and duration of stable disease will be summarized using Kaplan-Meier methods.

For the primary safety endpoint, AEs and serious adverse events (SAEs) will be tabulated by system organ class and preferred terms. Laboratory test results after the first dose will be summarized using change from baseline values and shift from baseline tables.

Each endpoint will be assessed both in the combined Cohorts and in each Cohort separately.

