## **2. STUDY OBJECTIVES**

The primary objectives of this study are as follows:

- To determine the confirmed response rate of GSK1363089 treatment in subjects with gastric carcinoma or adenocarcinoma of the gastroesophageal junction or of the distal esophagus.
- To further evaluate the safety and tolerability of GSK1363089.

The secondary objectives of this study are as follows:

- To assess the disease stabilization rate, progression-free survival, duration of stable disease, and overall survival in subjects with gastric carcinoma or adenocarcinoma of the gastroesophageal junction or of the distal esophagus who are treated with GSK1363089.
- To characterize the PK and pharmacodynamic parameters of GSK1363089 in subjects with gastric carcinoma or adenocarcinoma of the gastroesophageal junction or of the distal esophagus.

Note: Each of the primary and secondary study objectives will be assessed for each dosing Cohort (1 – Intermittent 5 days on/9 days off dosing; 2 – daily dosing) separately and together.

The exploratory objectives of this study are as follows:

- To characterize the *c-MET* amplification status of patients in this study population and possible associations with response to GSK1363089 therapy. In addition, the mutational status as well as expression of *c-MET* and related genes and proteins (e.g., RON) and of relevant downstream targets may also be assessed.
- To evaluate the efficacy and safety profiles between two GSK1363089 dosing regimens - Intermittent 5 days on/9 days off and daily.
- To evaluate the effect of GSK1363089 treatment on potential pharmacodynamic markers of clinical activity in paired tumor biopsies (e.g. phospho-MET).

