### **3.1.3. Treatment Extension Period**

In the absence of progressive disease (PD) and unacceptable toxicity, subjects may receive GSK1363089 treatment on the same dosing schedule for up to a total of 2 years at

the discretion of the investigator and beyond 2 years with the approval of the sponsor while participating in this study. Tumor assessment will continue approximately every 8 weeks while the subject remains on study.

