## 8.2. Determination of Sample Size

The trial will accrue 30 evaluable subjects in each Cohort, with or without confirmed c-MET amplification, as defined as  $\geq 3$  genomic copies of the *c-MET* gene. After the accrual of each cohort of 30 evaluable subjects, enrollment may be extended (to a maximum of 40 subjects) until at least eight subjects with confirmed c-MET amplification at 7q31, as defined as  $\geq 3$  genomic copies of the *c-MET* gene, are enrolled in each cohort. These will be stratified as follows:

- Stratum A: Subjects with confirmed *c-MET* amplification at 7q31.
- Stratum B: Subjects without confirmed *c-MET* amplification at 7q31

Additionally, as part of Amendment 4.0, there will be a requirement in Cohort 2 to have at least 4 evaluable subjects who meet a more stringent definition of *c-MET* gene amplification (i.e.  $\geq 2$  copies of *c-MET* per copy of chromosome 7; see Section 3.3.1 for a more detailed definition).

In the event that the enrolment of 30 evaluable subjects in Cohort 2 is completed before the target of 4 subjects with *c-MET* amplification, as defined by  $\geq 2$  copies of *c-MET* per copy of chromosome 7, has been reached, then extra subjects, with proven *c-MET* amplification, pre-screened by FISH, will be enrolled in the study, until the target is reached.

This sample size will allow an initial assessment of the tolerability of GSK1363089 in metastatic gastric cancer subjects, when dosed either in the intermittent 5&9 or daily schedules, building on the safety data from the two Phase I studies (77 subjects), which tested each of these schedules in subjects with a variety of solid tumors. Some hypothesis testing will also be possible with regards to the primary efficacy variable, which is the objective response rate (ORR), defined as the proportion of subjects for whom their best overall response is a confirmed CR or confirmed PR by RECIST:

For each Cohort, if at least 6 of the 30 evaluable subjects respond, this regimen of GSK1363089 will have demonstrated a response rate of 20%. This design is used to test the following hypothesis on the ORR:

Ho:  $P_o \leq 0.10$  versus  $P_a \geq 0.25$

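### Crude TEAE incidence over an open-ended, progression-dependent window can make the longer-treated regimen look more toxic; any comparison of the cohorts needs a fixed 8-week table

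*Combined protocol and SAP*

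**What the plan says.** Safety is one of the two primary objectives in Section 2: "To further evaluate the safety and tolerability of GSK1363089". A note there has each primary and secondary objective assessed per cohort and for the cohorts together. Among the exploratory objectives is "To evaluate the efficacy and safety profiles between two GSK1363089 dosing regimens".

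Section 8.1.4 describes the analysis. "Safety endpoints include adverse events, laboratory data, and concomitant medications". For adverse events, "TEAEs will be summarized for overall incidence, worst reported severity, and relationship to study treatment according to system organ class and preferred term". The counting window is closed by the rule "Only TEAE's with an onset date prior to date of last dose + 30 days will be tabulated in the summary tables". The synopsis (Statistical Methods) adds serious events: "For the primary safety endpoint, AEs and serious adverse events (SAEs) will be tabulated by system organ class and preferred terms". Laboratory values are graded by CTCAE and summarised as mean change and shift from baseline.

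Time on treatment is not fixed. Section 3.1.2 stops the drug at progression. Under Section 3.1.3, without progression or unacceptable toxicity, "subjects may receive GSK1363089 treatment on the same dosing schedule for up to a total of 2 years", and longer with sponsor approval. The cohorts are enrolled one after the other (Section 3.1).

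Section 8.1 leaves the details of the analyses to a separate SAP, whose text is not in the supplied documents.

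**The concern.** A proportion of subjects with at least one event has a clear meaning when everyone is observed for a similar time. Here the observation time is the time on drug plus 30 days, and time on drug depends on progression. A regimen that delays progression gives its subjects longer to record a first event or a worse grade.

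The protocol itself gives reasons why the cohorts might differ in time on treatment. Section 1.4.2 adds Cohort 2 partly to explore whether continuous exposure works better. Section 3.3.1 opens Cohort 1 to poorly differentiated tumours and Cohort 2 to a wider range of differentiation and to the distal esophagus. None of this shows that durations will differ, or in which direction. It does mean that the two columns of the planned TEAE table cannot be assumed to cover similar time at risk.

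At stake is the reading of the exploratory regimen comparison. A difference in crude incidence could be taken as a difference in toxicity when it reflects only time on drug, or a real difference could be masked.

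**Working it through.** The plan states no event rate, precision or expected treatment duration for safety, so there is no figure to reproduce. The check is an illustration on stated assumptions.

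**Inputs**
- From Section 8.1.4: counting window = time on drug + 30 days, with 30/7 = 4.286 weeks.
- From Section 3.1.2: an 8-week Study Treatment Period.
- Assumed: the same constant first-event hazard λ in both cohorts, also during the 30-day tail.
- Assumed: a share p with a first event by 8 weeks on drug, with p = 30% as the main case and 10% to 40% as the range.
- Assumed: durations of 12 versus 24 weeks, either fixed or exponential with those means.

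**Hazard.** λ = −ln(1 − 0.30)/8 = 0.0446 per week.

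**Fixed durations.** Crude incidence = 1 − exp(−λ(t + 4.286)).
- t = 12: 1 − exp(−0.726) = 0.516
- t = 24: 1 − exp(−1.261) = 0.717

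**Exponential durations, mean m.** Crude incidence = 1 − exp(−4.286λ) × (1/m)/(1/m + λ), with exp(−4.286λ) = 0.826.
- m = 12: 1 − 0.826 × 0.0833/0.1279 = 0.462
- m = 24: 1 − 0.826 × 0.0417/0.0863 = 0.601

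The gaps are 20 and 14 points with identical toxicity. If the hazard dropped to zero at the last dose, the tail would add nothing. The pairs would then be 41% versus 66% (1 − exp(−λt)) and 35% versus 52% (λ/(λ + 1/m)).

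**Range over p, tail included, same formulas**

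| p by 8 weeks | Fixed, 12 vs 24 weeks | Exponential, mean 12 vs 24 |
|---|---|---|
| 10% | 19% vs 31% | 18% vs 28% |
| 20% | 37% vs 55% | 34% vs 47% |
| 30% | 52% vs 72% | 46% vs 60% |
| 40% | 65% vs 84% | 57% vs 70% |

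**What an 8-week window does (p = 30%).** With fixed durations of 12 and 24 weeks nobody stops before week 8, and both cohorts show 30%. With exponential durations, the share stopping before week 8 is 1 − exp(−8/m): 49% for m = 12 and 28% for m = 24. Counting only events on drug, the 8-week incidence is λ/(λ + 1/m) × (1 − exp(−8(λ + 1/m))).
- m = 12: 0.349 × (1 − exp(−1.023)) = 0.223
- m = 24: 0.517 × (1 − exp(−0.690)) = 0.258

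So 22% versus 26%: the gap falls from 14 points to about 3, but not to zero. Dividing each by its mean on-drug time at risk in the window, (1 − exp(−8(λ + 1/m)))/(λ + 1/m), which is 5.01 and 5.78 weeks, returns 0.0446 per week for both.

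**The case against.** The strongest reply is that Section 8 is a protocol-level summary and defers detail to a separate SAP. Exposure, dose-modification and discontinuation tables are typical SAP content, and the list of safety endpoints need not be exhaustive. This stands for those tables: a reader might infer that such data are collected and never analysed, but the documents do not show that. Drug use and reasons for deviation are recorded (Section 6.5), as are dates and reasons for stopping (Section 14.4). The evaluable population (Section 8.1.1) already requires the share of mandated doses over 8 weeks and toxicity-related discontinuation to be worked out.

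A reader might also infer that tolerability goes unmeasured. It does not: worst severity, drug-relatedness, serious events and laboratory shifts are all planned.

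A third tempting reading is that the longer-treated or more active regimen *will* look more toxic, or that Cohort 1 must accrue more time because it started first. That needs durations to differ between cohorts and events to keep accruing. The documents give no durations, hazards or data cut-off, and early-onset events would be little affected.

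Finally, the comparison is exploratory, non-randomised and untested, between cohorts that already differ in histology and tumour site. Better tables will not make it clean. Per-cohort crude incidence is a legitimate description for what Section 8.2 calls an initial assessment.

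What survives is narrower. Section 8.1.4 does fix the TEAE measure and its window, and that measure mixes event rate with time on drug when the cohorts are set side by side.

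**Conclusion.** The point holds in conditional form. The only TEAE measure specified is crude incidence from first dose to last dose + 30 days, over treatment whose length is open-ended and depends on progression. If the cohorts differ in time on treatment, equal event rates can produce unequal incidence. For a doubling from 12 to 24 weeks, the illustrative gap is 12 to 20 points with fixed durations and 10 to 14 points with exponential durations, for p from 10% to 40%. These figures rest on a constant hazard carried through the 30-day tail and on assumed durations; they are not estimates for this trial.

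The effect is on the interpretation of an exploratory comparison, not on an error rate or on the primary response analysis. It merits a change to the analysis text because the remedy is cheap and the relative safety of the two regimens is something the study says it will address.

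**What to change.** Add to Section 8.1.4:

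1. A TEAE table, per cohort, of incidence and worst grade limited to onset in the 8-week Study Treatment Period, defined in calendar days from first dose so that dose delays do not move the boundary. Use this table for any statement about the regimens' relative safety.
2. Keep the full-period crude table as the descriptive summary, and show treatment duration per cohort beside it.
3. Because early stopping leaves a residual gap, report time on treatment within the 8 weeks, or analyse time to first event with stopping treatment as a competing event. In the latter case give the event-specific rate as well as the cumulative incidence, since on-drug cumulative incidence alone would still show the 22% versus 26% pattern above. State whether events after stopping but inside the window are counted.

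Summaries of dose intensity, dose reduction, delay and toxicity discontinuation over 8 weeks would be useful from data already recorded; confirm whether the separate SAP has them. Events per patient-month is optional: it assumes a roughly constant rate and can dilute early toxicity in subjects treated for long.

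The cost is a few extra tables and no change to conduct. The downside is that late-onset events fall outside the comparative table, so the full-period table must still be read for them.
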